### Statistical analysis

Data for all participants will be analyzed according to participants’ allocated group. A single formal analysis will take place at the end of the study. Interim data summaries will be made available to the independent data monitoring and ethics committee.

With regard to missing data, we shall aim to do the following 25: (1) implement strategies to limit the amount of missing data; (2) develop an understanding of the causes for data being missing and (3), based on this, decide what the main assumption about the mechanism of missing data is; (4) conduct a statistical analysis which accounts for this assumption; and (5) perform sensitivity analyses to assess whether the conclusions depend strongly on the validity of the main assumption about the mechanism of missingness.

### Clinical efficacy

Continuous outcome variables will be compared between treatment groups using a multilevel normal linear model. Change from baseline to outcomes (day 43; Fig. 1) will be modeled, adjusting for baseline value, time after stroke, and 9HPT score as patient-level covariates. Which therapist administered the treatment will be included in the model as a zero-mean random effect. We will test, by comparing the log-likelihood, whether a separate random-effect variance is required for therapists delivering each treatment arm or whether a pooled variance is sufficient. The treatment effect will be summarized using the adjusted mean difference and 95% confidence interval.

Secondary analyses will include sensitivity to incomplete follow-up, descriptive analysis at each time-point, statistical modeling of follow-up measures at six-months, and a per-protocol analysis. For safety analysis, the number and percentage of participants experiencing each prespecified category of adverse event will be summarized by treatment group.

### Neural correlates of response to CPT + FST and CPT + MPT

Our main intention with these analyses is to infer differences between correlations between neural explanatory measurements and CPT + FST and those between such measurements and CPT + MPT (objective 2). Associations will be investigated between change from baseline in clinical outcomes and change from baseline in each of the explanatory measurements. We will make every possible effort to record and adjust for potential confounding baseline variables, such as baseline motor score.

The relationship will be explored further via multilevel linear regression, which will include which therapist administered the treatment as a random effect., We will assess whether changes in neuroimaging and/or neurophysiological measures are strongly associated with clinical improvements in the individual participant and, in particular, whether such associations differ between the CPT + FST and CPT + MPT groups. We acknowledge the potential value of structural mean models (SMM)/causal inference (CI) and are aware of the additional complexity due to clustering in the design. Therefore, we will investigate an extension of SMM/CI as a potential exploratory analysis 26.

The relationship will be explored further via multilevel linear regression which will include therapist as a random effect. We will assess whether changes in neuroimaging and/or neurophysiological measures are strongly associated with clinical improvements in the individual participant and in particular whether such associations differ between the CPT+FST and CPT+MPT groups.

### Indicators of response to CPT + FST and CPT + MPT

Baseline measurements considered will be (a) TMS- and DTI-based measurements related to corticospinal system integrity, (b) normalized lesion maps, (c) voxel-wise measurements of gray and white matter density, (d) voxel-wise measurements of brain activity during hand grip and its modulation by changing force, and (e) clinical variables, including motor scores. An interaction term between treatment group and each variable from (a) to (e) in turn will be added to the normal linear model for ARAT used in the clinical efficacy analysis. Continuous baseline variables will be categorized as high or low, the cutpoint being at the median of the observed data. We will adjust for the time after stroke category. Statistical significance of the interaction term will be assessed and treatment effect calculated within each of the high and low sub-groups of the interaction variable.

Further analysis will develop a multiple regression model within each treatment group to predict change in ARAT clinical outcome using baseline measurements. This will determine the sub-set of baseline variables independently associated with treatment response and will allow for a different group of baseline predictors within each treatment group. Principal components analysis will be used to reduce dimensionality of the predictor variables while retaining a meaningful interpretation of the principal components.

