### Sample size

The clustered data structure (patients grouped according to therapist within each treatment group) is accounted for in the design and analysis 24. This sample size calculation is based on actual ARAT data from our previous early-phase trial 9. Assuming an intraclass correlation coefficient of 0·01 in both treatment arms and three centers with a separate therapist for each randomized arm, a sample size of 99 participants per group would have 80% power to detect a clinically important mean difference of 6·2 in ARAT change when data were analyzed using a two-sample *t*-test with Satterthwaite correction, applying a 5% two-sided significance level and allowing for potentially different standard deviations in the CPT + MPT (7·9) and CPT + FST (19·3) groups. To account for clustering in the design (participants grouped according to therapist within each randomized treatment at each study site), a sample size inflation factor, 1 + (*m*-1)*ICC, is applied, where *m* is the cluster size and ICC is the intraclass correlation coefficient. Assuming that recruitment is evenly distributed across therapists, sample size is therefore inflated to 129 evaluable participants per group. The corresponding mean differences in ARAT change that would be detectable in a study of this size for ICCs of 0·02 and 0·03 would be 7·0 and 7·8 respectively, showing that the design is fairly insensitive to assumptions about the ICC. Finally, to allow for an attrition rate of 10% [7% in our previous single-center trial 9], 144 participants per group will be recruited for a total sample size of 288.

For the explanatory measurements, our experience indicates that of those meeting the criteria for this proposed trial, at least 70% will consent to participate, and 90% of these will complete the measurements. Thus, we anticipate 181 sets of explanatory measurements.

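### Splitting each continuous baseline predictor at the sample median before testing its interaction with treatment costs about a third of the information if the predictor is roughly normal and its effect linear

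*Protocol article*

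**What the plan says.** The protocol article's section on indicators of response lists five groups of baseline candidates: corticospinal measures from TMS and DTI, lesion maps, tissue density, brain activity during grip, and clinical variables including motor scores. The test is then specified: "An interaction term between treatment group and each variable from (a) to (e) in turn will be added to the normal linear model" used for ARAT in the efficacy analysis. For predictors on a continuous scale the coding is fixed: "Continuous baseline variables will be categorized as high or low, the cutpoint being at the median of the observed data". After that, "Statistical significance of the interaction term will be assessed", and a treatment effect is given for the high and the low half.

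A second analysis in the same section builds a multiple regression for ARAT change separately in each arm, with principal components to reduce the number of predictors. No median split is stated for it.

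The Sample size section expects 181 sets of explanatory measurements.

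**The concern.** The third objective asks whether any pretreatment measure predicts improvement well enough to direct therapy to likely responders. The interaction model is the direct test of whether a measure changes the difference between the two therapies. Such tests are weak to begin with. Coding a continuous predictor as high or low before the test removes all variation within each half: a patient just above the median counts the same as the most extreme patient in the sample, and differently from a patient just below it. Where the true relation is smooth, this lowers the chance of finding a real effect modifier.

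The cutpoint is a second difficulty. The median of the observed data reflects the case mix of the patients recruited. Another sample would give another median, so a high/low result does not translate readily into a rule for future patients.

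**Working it through.** **Inputs.** From the Sample size section: "144 participants per group will be recruited for a total sample size of 288"; 70% consent to the explanatory measurements and 90% of these complete them; 129 evaluable per group. The 5% two-sided level is stated there for the primary comparison, and I assume it for each interaction test. The predictor's distribution and the shape and size of its effect are not in the article, so they are assumptions shown as a range.

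**Step 1, the plan's own figure.** 288 × 0.70 × 0.90 = 181.4, so the stated 181 reproduces.

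**Step 2, information kept.** With a linear effect, the share kept is the squared correlation between the predictor and its high/low indicator. It is 2/π = 0.637 for a normal predictor, 0.75 for a uniform one, and (ln 2)² = 0.480 for an exponential one.

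**Step 3, equivalent number of sets.** Normal: 181 × 0.637 = 115. To offset the loss, 181 / 0.637 = 284 sets would be needed.

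**Step 4, power.** Take an interaction with exactly 80% power when the predictor is continuous. After the split, power is Φ[(1.960 + 0.842) × √(share kept) − 1.960]. Normal: Φ(2.802 × 0.798 − 1.960) = Φ(0.275) = 0.61.

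**Step 5, simulation.** 181 independent patients in two equal arms, equal residual variances, 5,000 runs. The interaction slope was 2.8 × 2/√181 = 0.416 residual SD per predictor SD, since the standard error of the interaction is about 2/√n.

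| Predictor shape | Share kept | Loss | 181 sets act like | Power by formula, from 80% | Simulated power, continuous → split |
|---|---|---|---|---|---|
| Normal | 0.637 | 36% | 115 | 61% | 79% → 58% |
| Uniform | 0.750 | 25% | 136 | 68% | 80% → 67% |
| Exponential | 0.480 | 52% | 87 | 49% | 76% → 46% |

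A separate simulation used 90 per arm, the article's unequal SDs of 7.9 and 19.3, a normal predictor and an assumed interaction of 6.2 ARAT points per predictor SD. It gave 78% continuous against 59% split.

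**Step 6, type I error.** With no true interaction, the first simulation rejected in 4.7% to 5.2% of runs with the predictor continuous and 4.6% to 5.3% with it split. The split costs power and does not inflate the error rate.

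**Step 7, clinical predictors.** These are not limited to the 181 sets. With 2 × 129 = 258 evaluable participants, a normal clinical predictor split at the median acts like 258 × 0.637 = 164. The proportional loss is the same.

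None of these calculations models clustering by therapist.

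**The case against.** The strongest reply has four parts.

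- **The loss is conditional.** This stands. The 36% needs a normal predictor and a linear effect. The shapes tried give 25% to 52%, and a true step at the median would lose nothing. The article gives no reason to expect such a step.
- **The third objective does not rest on the interaction tests alone.** This stands as to scope: the abstract names a multiple regression as the way to find independent predictors, and no split is stated for it. It does not cure the problem, because that regression is fitted within each arm. It can describe who improves under each therapy but does not test whether a measure changes the difference between them.
- **The trial is meant to inform a later definitive trial, so no final cutpoint is needed yet.** This is fair, and makes the cutpoint argument secondary. It does not justify losing power now.
- **The analysis plan is not shown and may do better.** It may, but the split is a stated choice in the article and not a gap, so a plan that follows the article would carry it forward.

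A reader might also infer three stronger points, which the documents do not support:

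- **Uncontrolled false positives.** The variables are tested in turn and include "voxel-wise measurements of gray and white matter density", so one might conclude that nothing is corrected for multiplicity. The article gives neither a significance level nor a count for these tests and does not say they go unadjusted. Such detail is commonly left to the analysis plan. Nor does the split cause false positives (Step 6).
- **The rule fails for lesion maps**, because most voxels are unlesioned in most patients. That argument treats a voxel as lesioned or not, which is binary, whereas the rule covers continuous variables only.
- **Confounding remains within each half.** The contrasts are randomised treatment comparisons within baseline-defined sub-groups, and variation of the predictor inside a half does not confound them.

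**Conclusion.** The point holds for the treatment-by-predictor interaction analysis and for the median split only. For a roughly normal predictor with a linear effect, the loss is about 36% of the information: 181 explanatory sets act like about 115, and 80% power becomes about 61% by formula. Other predictor shapes move the loss between about 25% and 52%, and a step at the median removes it. These figures assume 5% two-sided tests and independent patients. The sample-specific cutpoint is a further, smaller reason against the split. The change should be made, because a better analysis of the same data is available at almost no cost. The within-arm regression, as described, is not affected.

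**What to change.** In the indicators-of-response section, and in the analysis plan if it repeats the rule:

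- enter each continuous baseline predictor as continuous in the interaction model, linear by default, and check the shape with a spline;
- base the test on that interaction term;
- report the estimated treatment effect with its confidence interval at centiles chosen in advance, such as the 25th and 75th;
- keep the high/low median sub-groups as a descriptive display only.

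No new data or participants are needed. The cost is slightly more analysis work and a linearity assumption that has to be checked and reported.

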Evaluation of FST through properly designed clinical trials is crucial. We are aware, however, that a potentially serious barrier to the development of any novel treatment for poststroke motor impairment arises from poor understanding of its mechanisms of action and, in particular, whether it is likely to work in all stroke sub-groups 10. The CIMT and RAT trials recruited patients based on clinical phenotype, but in order to target therapy to those most likely to benefit, this may not be sufficient. It is increasingly recognized that large rehabilitation trials need to include more sophisticated measures of residual brain structure and function in order for researchers to understand the mechanisms of action of treatment and the characteristics of ‘responsive’ patients 10,11. For example, both the pretreatment level of brain activity in primary motor cortex during the performance of a motor task 12 and the degree of damage to descending motor white matter pathways 13 were associated with greater clinical improvement in 24 chronic stroke patients undergoing two-weeks of robot-based therapy. These studies are encouraging, but if we are to incorporate such data into models that can accurately predict therapeutic response, larger sample sizes are clearly required.

Specific objectives of this trial are the following:
to determine whether CPT + FST commenced early after stroke produces greater improvements in upper limb motor recovery than CPT + MPT;to identify similarities and differences in the neural correlates of clinical improvement in response to (a) CPT + FST and (b) CPT + MPT;to determine whether any pretreatment parameters or combinations are sufficiently predictive of improvement in upper limb motor function in response to intervention to enable physical therapy to be targeted at those most likely to respond;to provide estimates of the preliminary cost-effectiveness of CPT + FST and inform the design of a subsequent pragmatic trial.

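### Objective 3 asks whether baseline measures predict well enough to target therapy, but the stated within-arm regressions yield only in-sample associations, with no optimism-corrected accuracy

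*Protocol article*

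**What the plan says.** The third specific objective (protocol article, Introduction) is to find out whether any pretreatment parameters, alone or combined, are "sufficiently predictive of improvement in upper limb motor function in response to intervention to enable physical therapy to be targeted" at likely responders.

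The section on indicators of response lists five families of baseline candidates: TMS and DTI measures, lesion maps, voxel-wise tissue density, voxel-wise brain activity with its modulation by force, and clinical variables. It first plans treatment-by-baseline interaction tests, one variable at a time. It then continues: "Further analysis will develop a multiple regression model within each treatment group to predict change in ARAT clinical outcome using baseline measurements". The purpose of that step is stated too: "This will determine the sub-set of baseline variables independently associated with treatment response". The sub-set may differ between arms, and principal components analysis (PCA) is to reduce the number of predictors.

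On numbers, the Sample size section says that "144 participants per group will be recruited for a total sample size of 288". For the explanatory measures it expects that "at least 70% will consent to participate, and 90% of these will complete the measurements", and concludes: "Thus, we anticipate 181 sets of explanatory measurements".

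The article mentions no hold-out sample, cross-validation, bootstrap, shrinkage or other correction for optimism. It also gives no number of candidates or retained components, no selection rule and no level of accuracy that would count as sufficient.

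**The concern.** Objective 3 is a question about accuracy in patients not yet seen, because only that accuracy can justify directing therapy. The stated method ends in a list of selected predictors and a fit computed on the participants who determined the list. Such a fit overstates accuracy: selection favours variables that happen to correlate with outcome in this sample, and least squares then fits their coefficients to the same noise. PCA lowers the number of candidates but does not remove the optimism of selecting and scoring in one data set.

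The Summary says the results should inform a definitive trial. Predictors that owe their place to chance, or real predictors with inflated accuracy, could be carried forward into that trial's targeting.

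**Working it through.** **1. Participants available (Sample size section).** 288 × 0.70 × 0.90 = 181.4, which reproduces the stated 181. Per arm this is 181.4 / 2 = 90.7, so n = 90 is used below. A model with clinical predictors only could use up to the 129 evaluable participants per group.

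**2. Chance of a spurious sub-set when nothing predicts.** The candidate count k and the entry level are assumptions. For k independent candidates entered at p < 0.05:

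- one arm: 1 − 0.95^k
- at least one of the two arms: 1 − 0.95^(2k)

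The one-arm formula was checked by simulating forward selection on pure noise (n = 90, 2000 replicates per setting).

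| k | One arm, formula | One arm, simulated | At least one arm, formula |
|---|---|---|---|
| 5 | 23% | 22.5% | 40% |
| 7 | 30% | 31.2% | 51% |
| 10 | 40% | 38.5% | 64% |
| 14 | 51% | 52.0% | 76% |
| 20 | 64% | 62.5% | 87% |

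A separate simulation with backward elimination gave 30%, 39% and 66% in one arm for k = 7, 10 and 20. The formulas do not contain n, so the larger sample for clinical predictors would hardly change these rates.

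**3. Sensitivity to the assumptions.**

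- Candidates correlated 0.5, p < 0.05: one arm 30%, 36%, 41% and 50% for k = 10, 14, 20 and 30; at least one arm 50%, 59%, 65% and 75%.
- Looser entry (p < 0.157, similar to AIC), independent candidates, 1000 replicates: one arm 57% at k = 5 and 82% at k = 10.

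**4. Size of the optimism.** In the forward-selection runs at p < 0.05 with independent candidates, for k from 5 to 30 and wherever something was selected, mean apparent R² was 0.06 to 0.12. The same models applied to new simulated patients had mean R² of −0.08 to −0.15.

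If all k candidates are kept, R² is always positive and its null expectation is k / (n − 1) = k / 89:

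- k = 5: 5 / 89 = 0.06
- k = 10: 10 / 89 = 0.11
- k = 20: 20 / 89 = 0.22
- k = 30: 30 / 89 = 0.34

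**5. Does correction work?** Ten-fold cross-validation with selection repeated inside each fold (400 null replicates per setting, independent candidates, p < 0.05) gave mean R² of −0.02 at k = 5, −0.05 at k = 14 and −0.12 at k = 30. It was positive in about 5% to 13% of replicates.

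**The case against.** The strongest objection is that much of this rests on silence. The article never says that in-sample R² is the criterion, and never says that any non-empty sub-set will be called sufficient. It refers to a statistical analysis plan and a fuller operational protocol, neither of which is shown; validation, the selection rule and the number of components could be set there. A reader might infer that the trial has decided to judge prediction on its development data. The documents do not support that. What stands is narrower: the method that the article does state, followed as written, cannot answer the objective it serves.

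A reader might also infer that a false sub-set will arise more often than not. That is not established either. At p < 0.05 with independent candidates it takes 14 candidates in a given arm, or 7 per arm if either arm counts. With five retained components the rates are 23% and 40%. With candidates correlated 0.5, the rate in a single arm stays below half up to 20 candidates. Nor does it add anything that a chosen sub-set has positive R², since any least-squares sub-set does.

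Two further points are fair. A null in which nothing predicts is a calibration case, not a forecast: baseline motor scores are among the candidates and may well predict change in ARAT. And the regression is a further analysis after the interaction tests. Those tests bear on targeting, but they take variables one at a time and give no prediction accuracy, so they do not fill the gap.

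**Conclusion.** The concern holds as a mismatch between objective and stated method. Objective 3 needs accuracy in new patients, while the planned regressions deliver selected in-sample associations from about 90 participants per arm, with no correction stated. The direction of the bias in apparent fit is certain; its size is not, because k and the selection rule are assumed. Across 5 to 20 independent null candidates at p < 0.05, the chance of a spurious sub-set runs from about 23% to 64% in one arm. For at least one arm it runs from about 40% to 76% across 5 to 14 candidates. Correlation lowers these figures and a looser entry level raises them. The finding does not depend on any one of these percentages, and it falls away if the unseen analysis plan already provides internal validation of the whole procedure.

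**What to change.** Answer objective 3 with optimism-corrected R² and prediction error, with an interval. Repeat the whole procedure (PCA, selection and fit) within each bootstrap sample or cross-validation fold, separately for each arm. This requires the candidate list and selection rule to be written down in advance, so that the procedure can be rerun identically. Report in-sample fit as descriptive only.

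Report alongside it the corrected accuracy of a model with only baseline ARAT, 9HPT and time after stroke, all of which the clinical efficacy model already adjusts for. This is a reference that shows what the imaging and TMS measures add. Requiring the fuller model to beat it would be one reasonable choice, but the objective does not entail it, so it need not be a decision rule.

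The cost is analysis-plan wording and computing time, with no new data. The reported accuracy will be less favourable.

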## Summary

This trial aims to determine clinical efficacy of CPT + FST and CPT + MPT for enhancement of upper limb motor function early after stroke, neuro-biomechanical correlates associated with clinical improvement, and which stroke survivors may be most likely to respond to FST and which to MPT. The results are expected to inform a subsequent definitive clinical trial and also to lead to advances in knowledge of how the upper limb recovers after stroke in response to well-characterized interventions.

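### The within-arm regressions are said to determine predictors of treatment response, but without a comparator they can only identify predictors of improvement under each therapy

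*Protocol article*

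**What the plan says.** Objective 3 in the Introduction asks whether pretreatment parameters, alone or in combination, predict improvement well enough "to enable physical therapy to be targeted at those most likely to respond". The Summary expects to learn "which stroke survivors may be most likely to respond to FST and which to MPT".

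The section Indicators of response to CPT + FST and CPT + MPT plans two analyses:

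- **Joint model.** A treatment-by-variable interaction is added to the ARAT efficacy model for each baseline variable in turn. Continuous variables are cut at the observed median. The interaction is tested, and the treatment effect is given in the high and low sub-groups.
- **Within-arm models.** A further analysis builds a multiple regression of ARAT change separately in each treatment group, with principal components to reduce the number of predictors. Its stated yield is: "This will determine the sub-set of baseline variables independently associated with treatment response and will allow for a different group of baseline predictors".

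The section states no comparison of coefficients between the two within-arm models. For the aim of finding independent predictors, the Abstract names only a multiple regression.

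On the data available, the Sample size section says: "Thus, we anticipate 181 sets of explanatory measurements".

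**The concern.** Response to a therapy is a contrast between what happens with it and what would have happened without it, or with the alternative. A regression inside one arm contains no such contrast. Participants are within 60 days of stroke and everyone receives conventional therapy, so ARAT change in an arm combines spontaneous recovery, conventional therapy and whatever the added therapy contributes. A variable that predicts this change may do so for purely prognostic reasons.

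The protocol's own account of the control makes the point sharper. It describes MPT as resting on approaches for which the evidence shows no effect against no treatment or placebo. On that premise, predictors found in the MPT arm would be largely prognostic, yet the plan labels them as associated with treatment response.

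The interaction tests are the right type of analysis for differential response, but each looks at one variable, and continuous variables are dichotomised. The claims about independent predictors, and about the combinations that objective 3 asks for, therefore rest on the within-arm models alone. If each arm returns a different list, a reader who wants to know whom to treat with FST and whom with MPT is likely to take the lists as the answer.

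**Working it through.** **1. Patients per model.** The Sample size section gives "144 participants per group will be recruited for a total sample size of 288" and, for the explanatory measures, "at least 70% will consent to participate, and 90% of these will complete the measurements". So 288 × 0.70 × 0.90 = 181.4, which reproduces the stated 181. Divided by 2, this is about 90 per arm.

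**2. Spread of the outcome.** The same section plans for "potentially different standard deviations in the CPT + MPT (7·9) and CPT + FST (19·3) groups". The equal-SD comparison uses √((7.9² + 19.3²)/2) = 14.75 in both arms.

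**3. One predictor, same true slope in both arms.** Nothing modifies the treatment effect here, so any apparent difference between arms is false. Take correlation 0.3 in the low-SD arm.

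- The slope per SD of the predictor is 0.3 × 7.9 = 2.37 ARAT points. In the high-SD arm the same slope is a correlation of 2.37/19.3 = 0.123.
- With n = 90 the noncentrality is r√88/√(1 − r²), which is 2.95 and 1.16. Power at two-sided 5% is 0.83 and 0.21.
- P(significant in one arm only) = 0.83 × 0.79 + 0.17 × 0.21 = 0.69. With equal SDs it is 2 × 0.83 × 0.17 = 0.28.

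Simulation (8,000 runs per setting) agrees:

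| Correlation (low-SD arm) | One arm only, equal SDs | One arm only, SDs 7.9 / 19.3 |
|---|---|---|
| 0 | 9% | 9% |
| 0.2 | 49% | 48% |
| 0.3 | 28% | 69% |
| 0.4 | 4% | 65% |
| 0.5 | 0.1% | 50% |

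In the same runs, a direct test of the slope difference was falsely positive in 4.5% to 5.4%.

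**4. Several predictors, same true slopes.** Simulation with 1,500 runs per setting, 90 per arm, independent predictors, ordinary least squares in each arm, and predictors kept at p < 0.05. R-squared is that of the low-SD arm. In the high-SD arm the same slopes give 0.3 × 7.9²/19.3² = 0.05 or 0.5 × 7.9²/19.3² = 0.08. The table shows how often the two lists differed.

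| Candidates (real) | Equal SDs, R² 0.5 | Equal SDs, R² 0.3 | SDs 7.9 / 19.3, R² 0.5 | SDs 7.9 / 19.3, R² 0.3 |
|---|---|---|---|---|
| 5 (3) | 19% | 49% | 95% | 98% |
| 10 (3) | 49% | 70% | 98% | 99% |
| 10 (5) | 56% | 96% | 100% | 100% |
| 20 (5) | 85% | 99% | 100% | 100% |

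- With the planning SDs, a real predictor was kept in 66% to 100% of low-SD-arm models but in only 14% to 36% of high-SD-arm models, although its slope was the same.
- The lowest cell is almost all noise. Two irrelevant candidates, each discordant with probability 2 × 0.05 × 0.95 = 0.095, give 1 − 0.905² = 18%. Real predictors were discordant in under 1% of those runs.
- With 129 per arm, the evaluable number for the trial as a whole, lists differed in 16% to 93% of runs with equal SDs and in 91% to 100% with the planning SDs.

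**5. What is assumed.** The protocol article does not give the number of candidates, R-squared or the selection rule. Therapist clustering is left out. The near-5% rate in step 3 is per interaction and compares like for like only with the one-predictor table.

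**The case against.** **The right analysis is already planned.** A reader might infer that objective 3 as a whole would be answered wrongly. The protocol does not support that. The joint-model interactions come first, and the within-arm models are called further analysis. This stands, and it confines the defect to the multivariable part. It does not remove it, because only the within-arm models address independent predictors and combinations.

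**Prediction under a given therapy is a fair aim.** The aims and the Abstract speak of predicting motor improvement, and a within-arm model can do that. This stands too. The models may stay, under an accurate name. What fails is the claim that they determine variables associated with treatment response.

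**The protocol does not say it will compare the lists.** This is correct. A reader might infer that differing lists will be treated as proof of different response profiles, but the text only allows them to differ. The risk lies in combining that allowance with the stated claim and the Summary's aim.

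**The size depends on assumptions.** A reader might infer that the lists are bound to differ. With few strong predictors and equal SDs they differed in only 19% of runs. The unequal SDs are planning values from one earlier trial, described as only potentially different. The simulation treats the whole gap as residual noise, whereas a larger SD under FST could partly reflect varying treatment effects. These points stand, so the results are given as a range. However, a joint model is still needed to tell the two explanations apart.

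**Overfitting.** One might add that the selected models will be judged on the data that chose them. The protocol does not say so. Selection rules and validation belong to an analysis plan that is not shown, so no point is made of it.

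**Conclusion.** The concern holds in a limited form. The statement that regressions within each arm will determine the variables independently associated with treatment response is wrong as a matter of design, whatever the simulation settings. These models identify predictors of ARAT change under each therapy. They cannot support the multivariable part of objective 3, or the Summary's aim of learning who responds to FST and who to MPT.

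The simulation adds that, at about 90 per arm, differing lists are likely even when nothing differs: 19% to 99% of runs with equal SDs and 95% to 100% with 7.9 and 19.3, under the assumptions listed. For a single predictor, significance in one arm only occurred in 0.1% to 49% of runs with equal SDs and in 9% to 69% with the planning SDs, against about 5% for the direct test.

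The primary efficacy comparison is unaffected, and the planned one-variable interactions remain a sound type of analysis. The change is worth making before analysis, because the results are meant to inform a definitive trial.

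**What to change.** 1. Describe the within-arm regressions as prognostic, meaning predictors of improvement under each therapy, and replace the wording about treatment response.
2. State that a difference between the two predictor lists is not evidence of differential response.
3. Add one joint ARAT model, built on the efficacy model, with the principal components already planned, kept continuous, and treatment-by-component interactions. Let the residual variance differ by arm. Report the differences in slope with confidence intervals as effect modification, and the main effects as prognosis. A single overall test of the interaction block avoids running many tests at 5% each.
4. Base any statement about who does better on FST than on MPT on that model. It estimates benefit of one therapy relative to the other. Neither this model nor the present design can isolate response to either therapy alone.

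The cost is a few sentences and modest programming. The downside is that the interaction estimates from about 181 participants will be visibly imprecise. That is the honest state of the evidence, and the separate lists would conceal it.
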